## Abstract

**Background:**

In many low- and middle-income countries, where tobacco use is common, tuberculosis is also a major problem. Tobacco use increases the risk of developing tuberculosis, secondary mortality, poor treatment compliance and relapses. In countries with TB epidemic, even a modest relative risk leads to a significant attributable risk. Treating tobacco dependence, therefore, is likely to have benefits for controlling tuberculosis in addition to reducing the non-communicable disease burden associated with smoking. In poorly resourced health systems which face a dual burden of disease secondary to tuberculosis and tobacco, an integrated approach to tackle tobacco dependence in TB control could be economically desirable. During TB screening, health professionals come across large numbers of patients with respiratory symptoms, a significant proportion of which are likely to be tobacco users. These clinical encounters, considered to be "teachable moments", provide a window of opportunity to offer treatment for tobacco dependence.

**Methods/Design:**

We aim to develop and trial a complex intervention to reduce tobacco dependence among TB suspects based on the WHO 'five steps to quit' model. This model relies on assessing personal motivation to quit tobacco use and uses it as the basis for assessing suitability for the different therapeutic options for tobacco dependence.

We will use the Medical Research Council framework approach for evaluating complex interventions to: (a) design an evidence-based treatment package (likely to consist of training materials for health professionals and education tools for patients); (b) pilot the package to determine the delivery modalities in TB programme (c) assess the incremental cost-effectiveness of the package compared to usual care using a cluster RCT design; (d) to determine barriers and drivers to the provision of treatment of tobacco dependence within TB programmes; and (e) support long term implementation. The main outcomes to assess the effectiveness would be point abstinence at 4 weeks and continuous abstinence up to 6 months.

**Discussion:**

This work will be carried out in Pakistan and is expected to have relevance for other low and middle income countries with high tobacco use and TB incidence. This will enhance our knowledge of the cost-effectiveness of treating tobacco dependence in patients suspected of TB.

**Trial Registration:**

Trial Registration Number: ISRCTN08829879

## Background

### Tobacco epidemic

Eight out of every ten smokers live in low- and middle-income countries[1]. In several of these countries, tobacco use is on the increase. Consequently, 70% of the projected mortality secondary to tobacco use is likely to be borne by low- and middle-income countries[1]. In addition, people die at an earlier age in such countries, causing the loss of 20-25 years of productive life[2]. Cost of cigarettes is relatively high in low- and middle-income countries compared to food and other essential commodities, resulting sometimes in their substitution. Therefore, tobacco use puts enormous burdens on countries' already ailing economies and contributes to existing impoverishment. The WHO Framework Convention on Tobacco Control (FCTC)[3] uses international law as a lever to establish policies to reduce both supply and demand for tobacco[4]. The key recommendations include offering help to people who want to quit tobacco use[5].

### Treating tobacco dependence

It has been suggested that at least 180 million deaths related to tobacco can be avoided by reducing current tobacco consumption by 50%. Surveys suggest that three out of four smokers wish to quit and one-third attempt to quit every year[6]. However, only 1-3% are successful if attempting on their own[7]. There is overwhelming evidence for the effectiveness and cost-effectiveness of a number of psychological and pharmacological treatments for tobacco dependence[8,9]. The evidence suggests that both behavioural and pharmacological therapies have the potential to double the quit rates among smokers and are highly cost-effective[10]. In low and middle-income countries, spontaneous quit rates are lower suggesting an even greater need for supporting people who wish to quit, and an opportunity to have a higher health benefit.

One of the several challenges in treating tobacco addiction in low- and middle-income countries is the lack of resources and governmental funding for the implementation of effective interventions. Many countries facing a tobacco epidemic are also confronting other challenges related to communicable diseases and nutrition-related disorders. Therefore, it may not be possible for countries with limited resources to shift priorities. However, existing programmes (such as TB control) can be utilised to extend their role to tobacco control with minimum investment. The WHO recommends integration of such tobacco cessation interventions into an overall policy on tobacco control and incorporation of these programmes into general health care[8].

### Tobacco dependence and tuberculosis

Smoking is closely related to tuberculosis (TB), another big killer. TB is a major public health issue in several countries where nicotine use has reached epidemic proportions. For example, 15% of all new TB cases in the world occur in China where nearly two thirds of men use nicotine[11]. Smoking prevalence is generally high among TB patients. In India, TB patients are three times as likely to be smokers than rest of the population[12].

A number of recent reviews have suggested that smoking is strongly associated with increased rates of both TB infection and TB disease [13-18]. Passive smoking is a particular risk factor especially in children. One study highlighted the high risk of acquiring TB infection among children who live with other adults who have had TB and were also exposed to second hand cigarette smoke[19]. Smoking leads to faster progression and poorer prognosis of tuberculosis[20]. In relation to TB outcomes, smokers are also less likely to adhere to TB treatment and more likely to relapse after successfully completing treatment according to some studies[14]. Smokers have also been shown to have a high risk of dying secondary to tobacco use[13,16]. Since the proportion of people using nicotine is very high in countries where TB is a major problem, even a modest relative risk amounts to considerable attributable risk of infection to the population[18]. In countries where TB is endemic and the vast majority of the population has been exposed to TB at some point in their life, tobacco use is likely to lead to progression or reactivation of TB infection. Patients, especially males, who are diagnosed with latent TB infection are less likely to adhere to their treatment and more likely to progress to full blown tuberculosis[21].

#### Treating tobacco dependence among TB patients and TB suspects

The association between TB and tobacco epidemic implies that addressing nicotine use in global TB control is likely to be beneficial for controlling TB as well as chronic diseases. It therefore makes sense that brief advice or any other available treatment for smoking cessation should be included in the management plan of TB patients. There are unmet opportunities for prevention and control of tobacco use among TB patients. During a typical course of treatment for TB, patients are in regular contact with health professionals for at least six months. Patients are considered to be more receptive to health education messages and willing to modify their health behaviour when they are ill[22]. Patients' contact with a health professional whilst they are being investigated for TB is considered as one of the "teachable moments" which is highly likely to trigger behaviour change[23]. Therefore, it makes sense to include advice and treatment on smoking cessation for all patients coming in contact with TB services and not just TB patients.

#### Research problem and justification

Before recommending TB programmes to incorporate identification and treatment of tobacco use, it is highly desirable and ethical to assess the feasibility of such an intervention. We found one such study conducted in Sudan that examined the feasibility of adding a simple cessation intervention to the general health care provision for TB patients in a poorly resourced health system[24]. The study found that the health professionals were willing and able to support a high proportion of TB patients (44%) in smoking cessation. There is no published research to our knowledge that has evaluated the cost-effectiveness of identifying and treating tobacco addiction among TB patients or TB suspects using a randomised controlled trial. Such research is highly desirable. It will assist programme managers and policy makers to see how such an integrated approach between the two programmes can be effectively and efficiently incorporated. We plan to conduct this study in Pakistan, a low income country with a high incidence of TB and a high prevalence of tobacco use[25]. Recent emphasis on both Tobacco and TB control provides a window of opportunity to evaluate innovative solutions for both public health problems and make these accessible to the population in Pakistan.

#### Research questions

1. What is the effect of a tobacco cessation intervention, based on WHO's 'five steps to quit' model, on patients' point and continuous abstinence from tobacco use? [Effect evaluation]

2. To what extent do the health professionals communicate risks of tobacco use and benefits of its cessation to their patients? What are their experiences and opinions about this strategy? [Process evaluation]

3. How do patients experience the intervention for tobacco addiction? [Ethical evaluation]

4. What is the incremental cost-effectiveness ratio of the intervention for tobacco addiction compared to usual care? [Economic evaluation]

### General Objectives

We aim to develop and trial a complex intervention to reduce tobacco dependence among TB suspects based on the WHO 'five steps to quit' model. Although this work will be carried out in Pakistan, we expect our findings will have relevance to tobacco control in other low and middle income countries.

### Specific Objectives

We will follow the Medical Research Council framework (see explanation in Methods section) for designing and evaluating complex interventions. Our specific objectives are:

1. To use qualitative methods to inform the development of an intervention based on WHO's 'five steps to quit' model (Phase I).

2. To develop and pilot this intervention which is likely to consist of: (a) an illustrative desk-guide (on patient assessment, education and treatment of tobacco dependence) and a training manual on this desk-guide for training of health professionals; and (b) leaflets for patients and others in the house containing information on the harmful effects of tobacco and advice on stopping its use, implying both cessation and prevention of tobacco use (Phase II).

3. To evaluate the incremental cost-effectiveness ratio of this intervention compared to usual care by estimating the proportion of people successfully quitting tobacco use (Phase III).

4. To determine barriers and drivers to the provision of treatment of tobacco dependence within TB programmes (qualitative component of Phase III).

5. To promote and support long term implementation of this intervention (Phase IV).

## Methods/Design

### Conceptual and theoretical framework

We propose to evaluate the cost-effectiveness of a multi-faceted intervention to control tobacco dependence, which by definition is a 'complex' intervention. Such interventions in general consist of several inter-connected elements which are all important for their functioning[26]. Therefore, it is difficult to specify an active ingredient in a complex intervention. Evaluation is generally difficult as complex interventions are not easy to define, develop, document, standardise and reproduce[27]. MRC has produced a framework which divides such evaluation into different phases that can be sequential or iterative. Each phase answers a specific question that leads to the next phase of the evaluation.

The objectives in our study align with different phases of this framework as follows:

1. Phase I will help us in identifying the likely behaviour change-elements in relation to tobacco use for the intervention especially the training package for professionals (desk-guide and training manual), and the information leaflet for patients.

2. Phase II will help in developing and piloting the intervention to allow us to refine and standardise it, test its feasibility in a resource-limited situation and test the feasibility of various (research and routine) data collection tools.

3. Phase III will consist of a cluster randomised trial to assess the effectiveness of the intervention, a costing study to assess its cost-effectiveness, and a subsequent qualitative study to identify barriers and facilitators in delivering the intervention.

4. Phase IV will identify key activities required to scale up the intervention.

### Objective 1

To use qualitative methods to inform the development of an intervention based on WHO's five steps to quit model (Phase I)

#### Key activities

From a health systems point of view, we would be interested in understanding the local health care context for delivering the intervention. This would involve issues like current working environment, staffing, and workload issues. We will also explore the possibilities of funding NRT and bupropion, their registration and addition to the essential drug list. We will do this through conducting a workshop with the Tobacco Control Programme and other stakeholders at the start.

We will use qualitative approaches to understand: (a) the extent to which health professionals particularly doctors currently convey risks of tobacco use and benefits of its cessation to their patients; (b) how they perceive their own role, knowledge, skills and confidence in conveying these messages; (c) how their own behaviour towards tobacco use is going to affect their attitude towards patients using tobacco and the advice they might offer; (d) which professional group would be most appropriate to provide the different elements of the package e.g. initial advice, motivation assessment, counselling, follow-up; and (e) what would be most useful form and content of training package and tools to support them in this process. Among patients, especially presenting to primary care with respiratory complaints, we are interested in understanding: (a) to what extent they currently understand the risk of tobacco use and benefits of its cessation; (b) in what form and detail they would like to receive such information from health professionals; (c) what kind of visual images will be evocative but also culturally appropriate if used in education materials; (d) what are their common misconceptions about tobacco use; and (e) what is their attitude towards smoking cessation aids including willingness to pay for NRT (f) do women and men respond differently to advice by physicians versus others, and by advisors based on gender

We will use focus groups to identify common themes as these allow participants to interact with each other and stimulate and generate themes which are sometimes not possible with interviews[28]. We are not only interested in "what they say they do" (their belief system) but also in "what they really do" (their behaviour). FGDs are particularly useful in this context as participants often challenge each other and therefore provide more in-depth understanding of inconsistencies between reported and actual behaviour. We are also interested in the social and cultural constraints that modify behaviour and are generally brought up in FGDs.

#### Settings

Focus groups will be conducted in health centres which will be participating in the subsequent phases of the study.

#### Participants

We will conduct two focus groups each from the following three categories of informants i.e. six focus groups in total. We will invite 6-8 participants for each focus group from the following:

1. Doctors

2. Nurses and health technicians (paramedical staff)

3. Patients (tobacco users) with respiratory symptoms (one with males and other with females)

#### Sampling

Purposive sampling will be used to understand the breadth of variation as well as the typical attitudes and behaviours among professionals and patients. We will try to have participants from similar social class and backgrounds to allow enrichment of the data with minimum censorship.

#### Data collection

FGD will be facilitated by the research officer who will use a FGD topic guide which will be piloted with a group of health professionals and patients in another health centre. FGD will be tape-recorded.

#### Data analysis

We will use a sequential focus groups and analysis process so that the later focus groups can be informed by and test themes emerging from the earlier focus group discussions. We will conduct an inductive analysis by indexing through generating codes and identifying themes from the narrative text. Analysis will be conducted in the original language to identify and link themes. All narratives will be analysed separately first, followed by comparing and linking themes generated during the analysis across narratives.

#### Outputs

1. A training package and tools (both format and content) which are context specific and are likely to ensure health professionals have the knowledge, skills, motivation and confidence to convey the risks of tobacco use and the benefits of cessation to patients.

2. Culturally appropriate messages and the form in which they are communicated to patients that is likely to challenge their misconceptions, answer common queries, provide the right depth of knowledge, their attitude towards smoking cessation aids including willingness to pay for them and motivation for them to modify their tobacco-related behaviour.

3. An understanding of health system constraints and drivers in delivering the intervention including possibilities of paying for NRT and bupropion

### Objective 2

To develop and pilot this intervention which is likely to consist of: (a) an illustrative desk-guide (on patient assessment, education and treatment of tobacco dependence) and a training manual on this desk-guide for training of health professionals; and (b) leaflets for patients and others in the house containing information on the harmful effects of tobacco and advice on stopping its use, implying both cessation and prevention of tobacco use (Phase II).

#### Key activities

These can be divided into development and pilot.

##### In the development

Two different processes will be used to develop products for health professionals (training module & desk-guide) and patients (illustrative education tool & leaflet) respectively. We will convene a "local working group" of national (Pakistani) experts in tobacco control, primary care, health systems and district health services management, the district TB programme coordinator and primary care physicians and paramedics. This group will use the nominal group technique (a face-to-face group process technique for gaining consensus)[29] to agree the form and contents of the training module and desk-guide. We will use a decision framework based on the usefulness and applicability of the interventions. We will commission a local professional media company to develop illustrative education tools and leaflet. We will make sure that the education tools are prepared to be appropriate for both urban and rural population acknowledging different patterns of tobacco use and literacy. If necessary, we will produce separate versions of such tools. The product specifications will be based on the outcomes of the focus groups. The final product will be reviewed and approved by the local working group.

With permission, we will also make use of any existing materials developed by other international agencies, research groups or countries (such as the UK) which can be adapted to the context defined in the previous phase. Once we have developed draft materials, we will get external review from other national and international experts in the field.

##### In the pilot

The intervention will be delivered in six health centres (three urban, three rural). A decision to include these centres in the main trial will be taken at the end of the pilot depending upon required alterations in the intervention. In these centres we will introduce new tobacco use registers/questionnaires including queries such as: (a) current tobacco use (yes or no); (b) amount of tobacco use; (c) whether the patient is willing to try to stop tobacco use (yes or no); and (d) whether the patient has been registered to receive "five steps to quit" intervention[30]. We will develop and use separate data collection tools for people registered to receive the intervention. This will include a patient card filled in for every tobacco user who is willing to try to quit and a register of all such patients[30]. This will help us in assessing the feasibility of all these modifications and additions. 25 consecutive attendees who consent to participate and meet the inclusion criteria will be recruited in each centre (n = 100) and offered the intervention. Training evaluation of health professionals, in-depth interviews with patients and health professionals, and observations of the health professionals delivering intervention, will be carried out to identify: (a) any structural or processes barriers to the implementation; (b) modifications required in the data collection tools and systems; and (c) any modifications required in the training package based on participant observation and training event evaluation; (d) any changes in the assigned roles of health professionals within the package; and (e) any modifications required in desk-guide, patient education tool and leaflets based on observation of care delivery and discussion with care providers.

We will also estimate the validity of the subjective assessment of abstinence by using a cotinine test (or CO test) on all participants at follow up during this pilot. Depending upon the validity, we will decide to either use cotinine test (or CO test) in the actual trial or just the subjective assessment as a proxy.

Ultimately, based on the results of this pilot, we will develop a final version of the various components of the intervention. We will also modify the process for delivering the intervention if necessary.

#### Outputs

1. A refined training module and an illustrative desk-guide on patient assessment, education and treatment of tobacco dependence for health professionals' use.

2. An illustrative education tool for patients

3. Leaflets for patients and others in the house containing information on the harmful effects of tobacco and advice on stopping its use which has been piloted

4. Additional leaflet for the patient's family that will include an explanation of the impact of second hand smoke on the patient and others

5. A revised and refined process for delivering the intervention in the study sites

6. Appropriate and revised data collection tools and systems.

#### The Intervention and its key components

FIVE STEPS TO QUIT - The Intervention Model: This is based on the evidence-based recommendations for treatment of tobacco addiction published by WHO in 2001[8]. The same approach is being advocated by IUATLD, National US guidelines and NICE in the UK[23,31]. This model relies on assessing personal motivation to quit tobacco use and uses it as the basis for assessing suitability for the different therapeutic options for tobacco dependence. Thus, the approach maximizes the efficient use of nicotine replacement therapy (NRT) and bupropion.

Key Components: We would like to develop components of the "Five Steps to Quit" intervention model on the basis of the following principles:

• Based on best available evidence and following an approach recommended by international agencies such as WHO and IUATLD[23].

• Can be delivered in primary care setting by non-specialist health care staff (doctors or other non-medical personnel) integrated in their routine healthcare provision.

The intervention model consists of five key steps

1. Asking about the status of nicotine use;

2. Advising about the benefits of stopping nicotine use;

3. Assessing the motivation to stop its use;

4. Assisting in stop attempts through various therapeutic options; and

5. Arranging follow-up

Examples of the specific components for each step of the intervention are given in Appendix 1; this is a general guide only and modifications will be made during the development of the intervention.

### Objective 3

To evaluate the incremental cost-effectiveness ratio of these interventions compared to usual care by estimating the proportion of people successfully quitting tobacco use (Phase III).

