#### Study Design

To deliver 'five steps to quit' intervention (with or without offering the therapeutic option), individual patients cannot be randomised to the intervention and control arms within health centres due to the possibility of contamination. The most suitable design to assess its effectiveness is a cluster randomised controlled trial (RCT). The overall design is summarised in the trial flow chart in Figure 1. We propose to have three arms in the trial: (a) control arm - usual care and an information leaflet; (b) intervention arm 1 - 'five steps to quit' that includes offering therapeutic option; and (c) intervention arm 2 - 'five steps to quit' that excludes therapeutic option). We propose to select a total of 33 diagnostic centres (11 at each control and the two intervention arms) and to recruit 50 patients with suspected tuberculosis (see the section on sample size below).

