#### Delivery of the intervention

We propose to use a systematic, standardised approach to deliver 'five steps to quit' to make it effective and equitable[30]. It is envisaged that the intervention will be primary delivered by the TB DOTS facilitator based in the diagnostic centre with the help and under the supervision of the primary care doctor (Table 1). He will assess patients' eligibility for the study and send them to the TB DOTS facilitator for further assessment. All eligible patients will be provided with verbal and written information about the study and invited to participate. Patients who agree to take part will be taken through different components of the 'five steps to quit' programme in two appointments. Patients in intervention arm 1 will also be offered therapeutic option (Bupropion) and such patients will be referred to the primary care doctor for assessing suitability and prescribing Bupropion.

**Table 1 T1:** Follow up and contacts with health professionals

Trial arms	First contact	FU at week 1	FU at week 5	FU at week 8	FU at week 25
Intervention 1 (brief psychological intervention + therapeutics)	Assess eligibility at the laboratory	TB DOTS facilitator	TB DOTS facilitator	TB DOTS facilitator	TB DOTS facilitator
	TB DOTS facilitator	Doctor	Doctor (if necessary)		
	Doctor				
Intervention 2 (brief psychological intervention only)	Recruitment at the laboratory	TB DOTS facilitator	TB DOTS facilitator		TB DOTS facilitator
	TB DOTS facilitator				
Control (usual care + leaflet)	Recruitment at the laboratory	TB DOTS facilitator	TB DOTS facilitator		TB DOTS facilitator
	TB DOTS facilitator				

The TB DOTS facilitators and primary care doctors will be given a training course (using training manual) on the "five steps to quit" programme on the use of desk-guide and focusing on[30]:

• The scientific basis of the intervention

• Techniques to enquire about the status of tobacco use

• Providing brief advice on the benefits of stopping its use through visual images

• Approaches to assess nicotine dependence and motivation to quit

• Using this motivation to propose various treatment options explaining their pros and cons

• Training in the use of available pharmacotherapies and other cognitive-behavioural strategies

• The procedure for follow-up and other technical and organisational aspects.

• Familiarity with the recording and reporting system such as revised records and new tools

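### The cost-effectiveness ratio is set against usual care only, so the plan has no step that shows whether adding bupropion to counselling is worth its extra cost

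*Protocol article*

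**What the plan says.** The Protocol article names the economic comparator in four places:

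- Objective 3 concerns the "incremental cost-effectiveness ratio of these interventions compared to usual care".
- Specific Objectives, item 3, reads "To evaluate the incremental cost-effectiveness ratio of this intervention compared to usual care".
- Research questions, item 4, asks "What is the incremental cost-effectiveness ratio of the intervention for tobacco addiction compared to usual care".
- The Hypothesis sets the package, with or without the drug option, against usual care plus the leaflet.

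Under Study Design, the article states "We propose to have three arms in the trial": "control arm - usual care and an information leaflet"; "intervention arm 1 - 'five steps to quit' that includes offering therapeutic option"; and "intervention arm 2 - 'five steps to quit' that excludes therapeutic option". Table 1 (Delivery of the intervention) describes arm 2 as the brief psychological intervention alone and arm 1 as that intervention plus therapeutics. Arm 1 also has doctor contacts and, for patients on treatment, a further visit at week 8.

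Outcomes defines the economic outcome as healthcare cost per person who has stopped at four weeks, built from treatment cost and staff time. It gives no amounts. Data analysis compares intervention with control at four weeks and speaks of two arms at six months. No section states an arm 1 v arm 2 comparison of effect, cost or ratio.

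**The concern.** The three arms are alternatives, and arm 1 is arm 2 with the drug option added. For such options, the useful ratio for each is the one against the next less costly option still in contention. Arm 1 v control blends the cost and effect of counselling with those of the drug. It tells a programme whether the full package beats doing nothing new, but not whether the drug should be part of the package.

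The protocol treats that second question as open. Under Objective 1 it will explore funding for NRT and bupropion and their addition to the essential drug list, and it lists the possibilities of paying for them as an output. In the trial, treatment packs come from the research budget, so another payer would be needed at scale-up. The design produces the data for an answer, but the stated objective does not call for it.

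**Working it through.** The documents give no cost and no cost-effectiveness ratio, so there is no planned figure to reproduce. The check asks how far arm 1 v control can differ from arm 1 v arm 2.

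**Inputs**

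- Control quit rate p0 = 10% and a single intervention rate of 20% (Sample size; Quit rates).
- Cited gains of 74% for brief advice and 94% for bupropion (Quit rates). I read these as relative gains, because 10% × 1.94 = 19.4%, close to the planned 20%. This is an assumption.
- c = extra cost per patient of arm 2 over control; d = extra cost per patient of arm 1 over arm 2. Neither is given, so d/c is shown as a range.
- The planning rates are for six months and the economic outcome is at four weeks. No four-week rates are given, so the six-month rates stand in for them.

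**Formula**

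F = [d/(p1−p2)] / [(c+d)/(p1−p0)] = [(p1−p0)/(p1−p2)] × d/(c+d)

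where p1 and p2 are the quit rates in arms 1 and 2. F above 1 means that arm 1 v control flatters the drug.

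**Results**

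First case: p2 = 10% × 1.74 = 17.4% and p1 = 19.4%, so the increments are 0.020 over arm 2 and 0.094 over control, and F = 4.7d/(c+d). The multiplicative case takes p1 = 10% × 1.74 × 1.94 = 33.8%.

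| Control / arm 2 / arm 1 | d=0.25c | d=c | d=2c | d=10c | ceiling |
|---|---|---|---|---|---|
| 10 / 17.4 / 19.4 | 0.94 | 2.35 | 3.13 | 4.27 | 4.7 |
| 10 / 15 / 20 | 0.40 | 1.00 | 1.33 | 1.82 | 2.0 |
| 10 / 17.4 / 33.8 | 0.29 | 0.73 | 0.97 | 1.32 | 1.45 |

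If both intervention arms reach the planned 20%, arm 1 v control is (c+d)/0.10, a finite figure. Arm 1 v arm 2 is d/0: with d above zero, arm 1 is simply dominated.

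**What F below 1 means**

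Arm 1 v control is a weighted average of the two steps, c/(p2−p0) and d/(p1−p2). F is therefore below 1 exactly when the second step is cheaper per quitter than the first, which is extended dominance of arm 2. In the multiplicative case at d=c:

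- arm 2 v control: c/0.074 = 13.5c
- arm 1 v arm 2: c/0.1636 = 6.1c
- arm 1 v control: 2c/0.2376 = 8.4c

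Arm 2 drops out, and 8.4c, the ratio against control, is the right one for arm 1.

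**Precision of arm 1 v arm 2**

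With 11 centres × 40 analysed and ICC 0.036, the design effect is 1 + 39 × 0.036 = 2.404, and the effective size is 440/2.404 = 183 per arm. For 19.4% v 17.4% the standard error is √[(0.174×0.826 + 0.194×0.806)/183] = 0.0405. A 95% interval is then about ±7.9 points around a 2.0-point difference, and two-sided power is about 7%. For 20% v 15% power is about 24%.

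**The case against.** The strongest reply is that these are one-sentence objectives in a journal article. None says that usual care is the sole comparator, and stepwise ratios and dominance rules are commonly left to an analysis plan. Data analysis does mention assessing smoking status by intervention category, and costs and therapy type are recorded, so nothing blocks the extra contrast. This lowers the cost of the change but does not remove the point. The comparator is named in the research question, both statements of the objective and the hypothesis, and an analysis that followed them faithfully would omit arm 1 v arm 2. The singular intervention in some places and the plural in Objective 3 leave it unclear whether the arms would be pooled; neither reading contains the step.

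A second reply is that arm 1 v control carries the cost of counselling as well as its effect, and validly answers the question of package against usual care. That is true, and it is why these contrasts may stay.

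Two stronger readings are tempting:

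- A reader might infer that the planned ratio misleads in either direction. It does not: where F is below 1, arm 2 is extendedly dominated and arm 1 v control is correct.
- A reader might infer that the drug will look several times better value than it is. The documents do not support that as an expectation. No costs are given, and no cited percentage is assigned to an arm. The first case is unfavourable to the drug, because it credits arm 1, which has both components, with bupropion's gain alone. There, a factor of 3 needs 4.7d = 3(c+d), that is d of about 1.8c.

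The low power of arm 1 v arm 2 is also a fair objection to making it the headline. It is a reason to show the interval, not to leave the contrast out.

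**Conclusion.** The point holds in a limited form. Usual care is the stated comparator for three nested, mutually exclusive options. Ratios against it alone cannot show whether the drug option is worth its added cost, and can leave dominance of arm 1 unseen. The clearest case rests on the plan's own 20% in both intervention arms plus the assumption that arm 1 costs more.

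The size cannot be fixed from the documents. Over the scenarios with a drug increment above zero, the factor runs from about 0.3 to a ceiling of 4.7. Only values above 1 mean that the planned ratio flatters the drug. On the cited gains read as relative increases, this happens once d exceeds c/3.7, about 0.27c; at 15% v 20%, once d exceeds c; with multiplicative effects, once d exceeds about 2.2c. The effectiveness comparisons with control are untouched.

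**What to change.** Reword Objective 3, with specific objective 3 and research question 4 to match, as a full incremental analysis of the three arms:

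- Order the arms by mean cost.
- Remove any option ruled out by simple or extended dominance.
- Report each remaining option against the next less costly remaining one.
- Whatever the dominance result, also show the arm 1 v arm 2 differences in cost and effect with intervals that allow for clustering.
- Keep the contrasts with usual care if wanted; where arm 2 is extendedly dominated, arm 1 v control is the main ratio for arm 1.
- State that arm 1 v arm 2 is not powered (about 7% for 19.4% v 17.4%).

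The cost is a change of wording and one more contrast from data already to be collected. No arm, visit or sample size changes. The drawback is a wide interval for the drug increment, and a ratio that may be unstable when that increment is close to zero.
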